### iPad Application Development

Three standardized scales to assess dementia and caregiver burden were developed into specialized monitoring apps for the iPad through Memorial University’s Distance Education, Learning and Teaching Support. The Cohen Mansfield Agitation Inventory [26], the Cornell Scale for Depression in Dementia [27] and the Caregiving Hassles Scale [28] were selected because they were designed to be completed by caregivers, and were appropriate to evaluate caregiver burden or domains of function for targeted management of moderate to late stage dementia. The scales are validated tools to assess agitation, depression and daily hassles associated with dementia care [28-30] and will be discussed in detail subsequently.

The apps will be pre-loaded onto iPads. The main screen of the app displays a list of questions (Figure 2, panel A). An error message appears if participants miss questions and a list of missed questions appears to direct participants (Figure 2, panel B). Login is managed by the Telegerontology team, so participants will not be required to enter username, password or server information when opening the apps (Figure 2, panel C). Permission to reproduce these scales was granted by the authors and acknowledgements were included on the administrative page of the app (Figure 2, panel C). Each participant will be assigned a unique anonymous ID linked to the study number, which will allow the Telegerontology physician to access information remotely from a secure web portal (Figure 3).

### Telegerontology Measurement Framework

A measurement framework was designed to include domains from The International Classification of Functioning, Disability and Health [31] and the Wilson-Cleary Conceptual Model of Patient Outcomes [32]. Assessments encompass the following domains: personal, environment, impairment, disability, participation, quality of life, and health care use. Outcome measures, clinical assessment tools, remote monitoring tools and circle of care measures to be administered at each time point in relation to the study objectives are described in Table 1.

### Outcome Measures

Primary and secondary outcomes will be collected at baseline (pre-), during the intervention, after the intervention (post), and 6- and 12-month follow up. Assessments will be completed by trained clinical personnel who are also members of the research team. First assessments will be completed during the home visit, with subsequent measures collected remotely. All data will be manually entered into SPSS for analysis. The study outcomes will be used to answer the primary research question regarding Telegerontology’s ability to enhance the caregiver/patient/PCP triad and thereby improve care “in place” for people with dementia.

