**Methods:**

This is a cluster randomized feasibility trial with four rural regions in the province of Newfoundland and Labrador, Canada (2 regions randomly assigned to “intervention” and 2 to “control”). The study population includes 22 “dementia triads” that consist of a community-dwelling older Canadian with moderate to late dementia, their family caregivers, and their Primary Care Physician (PCP). Over the 6-month active study period, all participants will be provided an iPad. The intervention is intended as an adjunct to existing PCP care, consisting of weekly Skype-based videoconferencing calls with the Telegerontology physician, and other team members as needed (occupational therapist, physical therapist etc). Control participants receive usual community-based dementia care with their PCP. A baseline (pre-) assessment will be performed during a home visit with the study team. Post intervention, 6- and 12-month follow-up assessments will be collected remotely using specialized dementia monitoring applications and Skype calls. Primary outcomes include admission to long-term care, falls, emergency room visits, hospital stays, and caregiver burden.

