**Conclusions:**

Results from this study will demonstrate a novel approach to dementia care that has the potential to impact both rural PCPs, family caregivers, and people with dementia, as well as provide evidence for the utility of Telegerontology in models of eHealth-based care.

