This paper describes a novel approach to rural community-based dementia care that combines the health care triad model of dementia care (patient, caregiver, and PCP) with an innovative Telegerontology intervention. Telegerontology is an approach using videoconferencing to connect an interdisciplinary team in a regional specialty center to people in rural communities. The aim of this study is to use Telegerontology in order to systematically detect and address care needs of people with dementia and their family caregivers, while augmenting PCP relationships with dementia patients and their families. The overall objective is to assist people with dementia to age successfully “in place.” Furthermore, findings from this study will be used to identify feasibility issues that will inform the design of a full-scale randomized control trial (RCT).

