### Study Design

#### Overview

The study was approved by the local research ethics authority. This is a cluster randomized feasibility trial assessing 4 rural regions (2 per study arm) comparing usual rural community-based dementia care to Telegerontology plus usual rural community-based dementia care. Using the opaque envelope method, the rural regions will be randomized to control or intervention after baseline assessment. The intervention will last 6 months with the measurement of outcomes taking place at baseline, after 6 months (post), with follow-up occurring 6 months (6-month follow-up) and 12 months (12-month follow-up) after cessation of the intervention.

The study population will include 22 “dementia triads” that consist of a community-dwelling older Canadian with moderate to late dementia, their family caregivers, and their PCP. The study will be carried out in communities located in rural areas of Newfoundland and Labrador, Canada but will be monitored remotely from the metropolitan city of St John’s, Newfoundland and Labrador. We define *rural* in this study to mean a community with less than 10,000 residents and a location that is greater than two hours’ drive from the metropolitan city, where specialist health services are located. Before randomization, recruitment will begin by enrolling PCPs from rural communities who will make initial contact with potential participants. Written informed consent will be obtained for every individual agreeing to participate in the study except in the case for an individual with advanced dementia who lacks capacity, in which case consent will be obtained from the substitute decision maker. Consent will be reviewed without the presence of the PCP in order to limit undue influence for participation in the study.

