### Sample Size Calculation

Sample size was calculated based on regional population statistics rather than for statistical power, targeting 2.5% of the population of community-dwelling dementia patients in the target region. Based on prevalence estimates, 98.5/1000 Canadians over 40 years of age have dementia with 34% living at home. The total population for the entire recruitment region of the present study is approximately 38,490 suggesting that the total population of community-dwelling dementia patents is approximately 1,289. Therefore, we aim to recruit 42 participants for inclusion in this study accounting for a 30% dropout rate.

**Table 2 table2:** Occupational Therapy Home Safety Video checklist.

Video	Description
1	A short video walking from the driveway outside, going into the house through the usual entry door, straight through the kitchen/living area into the person's bedroom and then into the bathroom.
2	Kitchen (short video)
3	Bedroom (short video)
4	Bathroom (short video)
5	Living room (short video)
6	Stairs (short video)
7	Laundry (short video)

Qualitative interview questions.PCP Interview QuestionsDescribe the care required to manage people with dementia in their homes.From your point of view, how well are your patients being managed at home?How would you envision an ideal circle of care to maintain people with dementia in their homes?Caregivers Interview QuestionsFrom your point of view, how well are you managing the health of your loved one at home?In an ideal world, how could things be improved? What are the main challenges you experience? Have you had successes caring for your loved one?

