### Statistical Analysis

Data entry, consistency check, and cleaning will be performed prior to analysis. Mean and standard deviation will be used for continuous variables, while frequency and percentages will be used to describe categorical variables. We do not anticipate this study will detect statistically significant findings however, as part of a secondary analysis, unpaired *t* tests will be used. Differences between intervention and control groups with respect to outcomes will be compared using repeated measures ANOVA or independent *t* test split by group. Data analysis will be conducted using SPSS statistical software. A *P*<0.05 will be used to determine potential significance. The 95% CI for differences will also be calculated. With respect to dropout, every person who is randomized regardless or subsequent fall, death, or admission to LTC will be included in the final analysis. If participants drop out before the intervention or voluntarily withdraw they will not be included in the final analysis. For analysis of the clinical assessments tracked over the course of the study (schedule of assessment described in Table 1), intention-to-treat analysis will be used by carrying the last observation forward.

Qualitative analysis will follow the Framework Method [47]. This method helps build rigor and trustworthiness in qualitative analysis by providing a clear audit trail from the original data to the final themes including illustrative quotations.

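### An unpowered feasibility trial of two against two regions uses five effectiveness primaries, compared at P<0.05 without a region term, to answer a question the design cannot resolve

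*Protocol article*

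**What the plan says.** Several parts of the protocol article describe a feasibility study:

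- Study Design, Overview: "This is a cluster randomized feasibility trial assessing 4 rural regions (2 per study arm".
- Introduction: "findings from this study will be used to identify feasibility issues that will inform the design of a full-scale" trial.
- Sample Size Calculation: "Sample size was calculated based on regional population statistics rather than for statistical power".
- Statistical Analysis: "We do not anticipate this study will detect statistically significant findings".

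Other parts describe an effectiveness study. Objective 1 is to test whether the intervention strengthens the triad and so improves care at home. The Outcome Measures section states: "The study outcomes will be used to answer the primary research question", and defines that question as the same one. The Abstract lists the outcomes that carry this: "Primary outcomes include admission to long-term care, falls, emergency room visits, hospital stays, and caregiver burden". The two secondary outcomes, specialist referrals and PCP visits, are also utilisation counts.

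For analysis, the plan gives descriptive summaries first. It then compares arms by repeated measures ANOVA or independent t tests, with P<0.05 as a marker of possible significance and 95% CIs for differences. It presents the unpaired t tests as secondary. No term for region is named, although region is the unit of randomisation.

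**The concern.** The outcome hierarchy and the design point at different questions. The design can show whether a full-scale trial is workable and what it would need. The primary outcomes and the sentence on their use ask whether the intervention works. If the plan is followed as written, the report will carry P values and intervals that treat patients as independently randomised, and the text commits those results to an effectiveness question. One P<0.05 could then be read as support and a set of null results as failure, and neither reading would be sound. The feasibility findings, which are the useful product of this design, have no named place among the primary or secondary outcomes.

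**Working it through.** **The plan's own figure.** The only sample size arithmetic is in Sample Size Calculation. 38,490 × 0.0985 × 0.34 = 1,289; 1,289 × 0.025 = 32.2; 32.2 × 1.30 = 41.9, so 42. The target reproduces, and no effect size, variance, intracluster correlation (ICC) or power enters it. The Abstract and Overview give 22 triads instead, so both sizes are carried below.

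**What two against two regions can show.** The number of ways to allocate four regions, two per arm, is C(4,2) = 6. The smallest two-sided exact permutation P is 2/6 = 0.33. More patients in the same four regions do not change this.

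A cluster-level t test on region means can give smaller P values, but only by assuming normality, and it has 2 degrees of freedom. The article gives no effect size or ICC, so the following are assumptions: standardised difference d = 0.8, two-sided 0.05, ICC 0.01 to 0.10.

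| Total N | Power, t test ignoring clustering | Power, region-level test (2 df) |
|---|---|---|
| 22 (11 per arm) | 43% | 16–19% |
| 42 (21 per arm) | 72% | 20–30% |

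Ignoring clustering, 80% power needs d of about 1.26 at N = 22 and about 0.89 at N = 42.

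**False positives.** With k independent valid tests at 0.05, the chance of at least one false positive is 1 − 0.95^k.

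- k = 5 (five primaries, one time point): 1 − 0.95^5 = 22.6%.
- k = 15 (five primaries at three post-baseline times): 1 − 0.95^15 = 53.7%. This is an upper figure for valid tests, because repeated measures on the same people are positively correlated.

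Five-test figures when region is ignored were simulated with normal outcomes, individual-level t tests, two regions per arm of 6 and 5 (N = 22) or 11 and 10 (N = 42), and correlation between outcomes of 0 to 0.5. Ranges run over that correlation.

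| Assumed ICC | N = 22 | N = 42 |
|---|---|---|
| 0 | 19–23% | 19–23% |
| 0.01 | 20–25% | 22–27% |
| 0.05 | 27–34% | 35–43% |
| 0.10 | 35–43% | 50–60% |

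Several of the real outcomes are counts and one is a date of admission, so these figures show direction and rough size only.

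**The case against.** The strongest reply is that the plan already hedges. It opens with descriptive summaries, labels the t tests secondary, treats P<0.05 as potential significance only, plans 95% CIs, and concedes the small sample under Study Strengths and Limitations. Piloting the intended clinical outcomes is a legitimate aim of a feasibility trial. Multiplicity rules and progression criteria commonly sit in a full protocol or analysis plan that is not shown, so their absence here is no fault.

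Most of that stands, and it rules out four stronger readings:

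- *Chance positives are likely.* Five independent tests give 23%, so roughly three times in four there would be none. The 54% figure needs fifteen independent tests. The plan does not commit to these: ANOVA would take the time points in one model per outcome, and admission to long-term care is a date.
- *The article claims proven efficacy.* The Abstract does say "Results from this study will demonstrate a novel approach to dementia care", but the sentence goes on to speak only of potential impact.
- *Feasibility is ignored.* It is part of objective 2. Table 1 maps most clinical tools to that objective, and also the Caregiving Hassles Scale, itself a primary outcome. The time log has a stated feasibility use.
- *Primary outcomes can simply be swapped.* The Results section says data collection ended in April 2017, so that would be a post hoc change.

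The hedges do not remove the conflict. The Outcome Measures section still assigns the outcomes to an effectiveness question that the Statistical Analysis section does not expect to settle. The planned intervals are also not described as allowing for region.

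**Conclusion.** The point holds as an inconsistency within the article, together with a method of comparison that does not match the unit of randomisation. The conflict follows from the text alone. That the design cannot answer the effectiveness question rests on the permutation floor of 0.33, which needs no assumed effect size or ICC; the power figures support it under the assumed d and ICC. The false-positive risk is inflated rather than likely: about 23% for five independent valid tests, about 19–21% with correlations of 0.3 to 0.5, and more if regions differ and this is ignored. The change is worth making because it is cheap and governs how the results will be read.

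**What to change.** 1. In Statistical Analysis, drop the P<0.05 rule for between-arm comparisons. Report the five outcomes as exploratory estimates with 95% CIs that account for region.
2. Reword objective 1, the sentence on use in Outcome Measures, the Abstract conclusions and the closing Conclusion so that these results inform the design of the full-scale trial and do not answer an effectiveness question.
3. Make the feasibility data already gathered the main basis for conclusions: recruitment, dropout, app completion (visible in the web portal) and the team time log. Report delivery of the weekly calls only if calls were logged; the article does not say so.
4. Reconcile 22 triads with 42 participants before reporting recruitment against target.
5. Keep the five outcomes visibly labelled as the primaries originally named, and disclose the change of emphasis as dated and post hoc, since data collection is complete.

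No new data are needed. The cost is wider intervals, softer efficacy statements and an open note of a late change.

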**Figure 1 figure1:**
[figure not shown]
Study flow. After PCP recruitment, participant referrals and home assessment, the rural regions will be randomized to control or intervention.

**Figure 2 figure2:**
[figure not shown]
(A) Main screen display, (B) Error message for missing responses, (C) Administrative login page.

**Figure 3 figure3:**
[figure not shown]
Screenshot of secure web portal. Colored calendar blocks indicate days when app is completed by caregiver. Scores from reports are displayed by clicking on a colored block.

#### Primary Outcomes

Primary outcomes will be reported by caregivers and confirmed through medical records and chart reviews (schedule of assessment described in Table 1). Based on Canadian incidence rates, we anticipate these outcomes will be detectable during the 18-month study period [33-35]. The primary outcomes will be as follows:

Admission to long-term care (LTC): Date that participant is admitted to LTC.Emergency room (ER) visits: Total number of ER visits over 6 months.Falls: Total number of falls over 6 months.Hospital stays: Total number of hospital stays over 6 months.Caregiving Hassles Scale: This 42-item scale assesses the daily burden of caring for a family member with dementia. Caregivers are asked to rate patient requirements and behaviors on a 5-point scale of frequency, ranging from “Did not occur” to “A lot.” High scores indicate higher level of caregiver burden. Assessment takes 20 minutes to complete [28]. Administered by iPad, at pre, post, 6- and 12-month measures, in addition to an outcome measure, this scale will be used as a monitoring tool during the intervention at the discretion of the Telegeronology physician.

#### Secondary Outcomes

The secondary outcomes will be as follows:

Referrals: Total number of referrals to specialist care over 6 months.PCP visits: Total number of PCP visits over 6 months.

### Clinical Assessment Tools

These tools will be used to help characterize the progression of dementia throughout the study and to inform clinical decision making (schedule of assessment described in Table 1). These assessments will also be used to address feasibility issues and to inform remote monitoring practices. All assessments will be administered by the physician or physiotherapist.

#### Demographics and Medical History

Demographic information including age, sex, marital status, educational background, and living situation will be collected along with information about the patient’s circle of care. Medical information including allergies, comorbid diagnoses, medications, consultations, laboratory reports, details of the dementia diagnosis, and results of previous tests and assessments will be collected by chart review.

**Table 1 table1:** Measures mapped to study objectives and schedule of assessment.

Measure		Schedule (Stage)									
		Baseline		During intervention		Post assessment		6-month follow-up		12-month follow-up	
**Outcome Measures**											
	Emergency room visits^a^						✓^b^		✓		✓
	Hospital stays^a^						✓		✓		✓
	Admission to LTC^a,c^						✓		✓		✓
	Falls^a^						✓		✓		✓
	Referrals^a^						✓		✓		✓
	PCP visits^a,d^						✓		✓		✓
	Caregiving Hassles Scale^a,e^		✓		✓		✓		✓		✓
**Clinical Assessment Tools**											
	Demographics and medical history^e^		✓								
	Barthel Index of Activities of Daily Living^e^		✓								
	Timed Up and Go test^e^		✓								
	Kettle test^e^		✓								
	Face washing functional task^e^		✓								
	Custom Caregiver Quality of Life Index^e^		✓								
	Global Deterioration Scale^e^		✓				✓		✓		✓
	Mini Mental Status Exam^e^		✓				✓		✓		✓
	Montreal Cognitive Assessment^e^		✓				✓		✓		✓
	Occupational therapy home video assessment^e^		✓								
	Cohen Mansfield Agitation Inventory^e^		✓		✓		✓		✓		✓
	Cornell Scale for Depression in Dementia^e^		✓		✓		✓		✓		✓
	Telegerontology time tracking^e^				✓						
	Qualitative interviews (caregivers and PCPs)^f^		✓								

^a^Test Telegerontology’s ability to enhance the caregiver/patient/ PCP triad and thereby improve care ‘in place’ (ie, health care utilization) for people with dementia.

^b^✓=Performed at time point.

^c^LTC: Long-term care.

^d^PCP: Primary care physician.

^e^Assess and optimize a remote monitoring method for managing care of people with moderate- to late- stage dementia living at home in rural Canada in order to inform the design of a full-scale randomized control trial.

^f^Explore issues related to care of people with dementia from the caregivers’ and primary care physicians’ perspectives.

#### Barthel Index of Activities of Daily Living

The Barthel Index assesses self-care, mobility, and activities of daily living. It is widely used in geriatric assessment settings. Information is collected from observation, self-report or informant report. It takes approximately 5-10 minutes to complete. Maximum score is 100, indicating complete independence. Low scores on individual items highlight areas of need [36].

#### Timed Up and Go Test

The Timed Up and Go test assesses mobility, balance, walking ability, and fall risk in older adults [37]. When the assessment begins, the patient sits in the chair with his/her back against the chair back. On the command “go”, the patient rises from the chair, walks 3 meters at a comfortable and safe pace, turns, walks back to the chair, and sits down. Timing begins at the instruction “go” and stops when the patient is seated. The time (sec) between the command to start and when the buttocks touch the chair is collected. The patient should have one practice trial that is not included in the score and must use the same assistive device each time he/she is tested to be able to compare scores. The Timed Up and Go takes less than 5 minutes to administer [37]. Minimal detectable change in Alzheimer’s disease has been reported as 4.09 seconds [38].

